### Primary outcome analysis

Mortality until 90 days will be tested using mixed-effects Cox proportional hazard models, considering sites as the random variable (frailty models)^(3)^ adjusted for age, baseline SOFA^(4)^ score and the type of admission (planned admission, unplanned admission with baseline sepsis and unplanned admission without baseline sepsis). Sepsis will be defined as infection plus organ failure as per the Sepsis 3 criteria.^(2)^ Proportionality of the hazard ratio will be assessed using the Grambsch and Thernau method,^(5)^ and interactions between the intervention arms (infusion solution and speed) will be tested on this model. If the interaction parameter is significant, we intend to report only one manuscript describing “inside the table” effects, that is, exploring all the four possible combinations and their effects on mortality. If the interaction parameter is not significant at the 5% significance level, marginal effects for each group will be highlighted. In this case, “inside the table” effects shall be reported as supplementary material following CONSORT recommendations for 2 × 2 factorial designs.^(6,7)^ Kaplan-Meier curves will be presented comparing the four arms and separated considering only Plasma-Lyte® *versus* Saline, and Slow *versus* Rapid infusion. Patients with missing follow-up at 90-days will be added to the main primary outcome analysis and censored at their last known follow-up time, patients without discharge information will be imputed by chained equations method using site, age, baseline SOFA score and type of admission.

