Total SOFA score will be missing if patients died before the measurement time point , and multiple imputation by chain equations using the *mice* R^(10)^ package shall be performed to address the competitive risk bias. Acquired SOFA trend and baseline characteristics will be considered to predict any missed SOFA scores at 3 and 7 days, with the study arms as covariates. Sensitivity analysis without the arms as covariates shall also be performed.

Mechanical ventilation-free days within 28 days will be tested considering the proportion of ventilator-free days in that time frame using zero/one inflated beta or beta-binomial regression assuming zero free-days for those patients who died within that period independently of the amount of time the patient actually used the ventilator. We will consider as ventilation day any day where the patient received any duration of mechanical ventilation. Effect measures shall be presented as the absolute mean difference.

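### The imputation of the primary outcome omits both randomised arms and their product, so imputed patients pull the hazard ratios and the interaction toward the null by roughly the fraction imputed

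*SAP article*

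**What the plan says.** All of this is in the SAP article. Under Primary outcome analysis, the primary model is set out as follows: "Mortality until 90 days will be tested using mixed-effects Cox proportional hazard models, considering sites as the random variable". It is adjusted for age, baseline SOFA and type of admission. On the two interventions the section adds that "interactions between the intervention arms (infusion solution and speed) will be tested on this model". The result steers the reporting: "If the interaction parameter is not significant at the 5% significance level, marginal effects for each group will be highlighted". If the interaction is significant, the four combinations become the main report.

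The same section gives two rules for incomplete outcome data. The first is "Patients with missing follow-up at 90-days will be added to the main primary outcome analysis and censored at their last known follow-up time". The second is that patients whose discharge information is missing are to be "imputed by chained equations method using site, age, baseline SOFA score and type of admission". The second list is specific, and neither arm is on it. The section does not say which variable is imputed (vital status, time of death or discharge date), or which rule comes first for a patient who meets both.

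Under Secondary outcomes, missing total SOFA scores are also imputed by chained equations, but there "with the study arms as covariates". The version without the arms is only a sensitivity analysis. The section on sensitivity analyses lists none for the imputation of the primary outcome.

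**The concern.** An imputation model should contain the terms that the analysis model estimates. Here the analysis estimates fluid, speed and their interaction, and the imputation model contains none of them. An outcome drawn from site, age, SOFA and admission type alone is, given those covariates, unrelated to allocation. When such patients are pooled with the observed ones, both treatment effects and the interaction are diluted.

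Two things are at stake. One is power for the two main comparisons. The other is the interaction test, because it decides whether marginal or four-cell effects lead the report, and dilution tips that choice toward marginal effects. The dilution would also mute harm as much as benefit, in a trial meant to give evidence in either direction.

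**Working it through.** **Inputs.** From the sample size section: 11,000 patients, 35% control mortality at 90 days, hazard ratio 0.9, stated power 89%. From the study background section: 1:1:1:1 allocation, hence 5,500 per side of each marginal comparison. From the planned analysis section: alpha 5%, taken as two-sided to match the 95% intervals. Not in the article and therefore assumed: the imputed fraction m (1%, 2%, 5%, 10%) and, for the interaction, a ratio of hazard ratios of 0.80.

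**Step 1, reproduce the stated power.** Treated risk = 1 − 0.65^0.9 = 0.3214. Events = 5,500 × (0.35 + 0.3214) = 3,693. Power = Φ(√(events/4) × |ln HR| − 1.960) = Φ(√(3,693/4) × 0.10536 − 1.960) = Φ(1.241) = 89.3%. If both interventions work, events fall to 3,540 and power is 88.0%. The stated 89% is reproduced.

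**Step 2, dilution.** With a fraction m imputed without the arms, the pooled log hazard ratio is about (1 − m) × θ + m × 0 = (1 − m)θ. The same holds for the interaction.

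**Step 3, power at equal missingness.** The fair comparator is an analysis with the same m and the arms included. It also loses information, but it is not diluted.

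- Arms omitted: Φ(√(3,693/4) × (1 − m) × 0.10536 − 1.960)
- Arms included: Φ(√(3,693 × (1 − m)/4) × 0.10536 − 1.960)

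| m | HR estimated, arms omitted | Power, omitted | Power, included | Loss due to omission (points, before rounding) |
|---|---|---|---|---|
| 1% | 0.901 | 88.7% | 89.0% | 0.3 |
| 2% | 0.902 | 88.0% | 88.7% | 0.6 |
| 5% | 0.905 | 86.0% | 87.7% | 1.7 |
| 10% | 0.910 | 82.2% | 85.9% | 3.8 |

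With the arms included the hazard ratio stays at 0.90. The omitted-arm column uses the complete-data standard error. This is a simplification that favours the omitted-arm analysis, because multiple imputation would add a between-imputation component.

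**Step 4, interaction.** With variance 16/events and a true ratio of hazard ratios of 0.80, power omitted versus included is 91.9% vs 92.1% at 1%, 91.3% vs 91.9% at 2%, 89.6% vs 91.1% at 5% and 86.2% vs 89.5% at 10%. The estimated ratio moves from 0.80 to 0.802, 0.804, 0.809 and 0.818.

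**Step 5, check by simulation.** The design was a 2×2 trial with a binary outcome missing completely at random, 44,000 patients, 60 replicates and 5 imputations. At 10% imputed, the two main effects and the interaction came out at 0.91, 0.90 and 0.88 of the truth with the arms omitted, and at 1.00, 1.00 and 0.99 with them included. The runs at 2% and 5% were noisier. Both methods saw the same data sets, so dividing omitted by included removes much of the shared noise. This gives 0.98, 0.98, 0.98 at 2% and 0.96, 0.95, 0.94 at 5%, in line with 1 − m.

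**The case against.** The strongest reply is that the affected group is narrow. A patient who merely lacks 90-day follow-up is "censored at their last known follow-up time", and only those whose discharge information is missing are imputed. Nothing in the article suggests that this group reaches 5% or 10%. At 1–2% the estimated hazard ratio moves only from 0.900 to 0.901 or 0.902. The shift is also conservative for a superiority hypothesis: with no true effect, imputing without the arms imposes nothing false, so type I error is not inflated. All of this stands, and it limits the point. It does not remove it, because the omission is explicit and no other section repairs it.

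A reader might infer four stronger things that the article does not support.

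- *That the omission takes power from 89% to 82%.* That compares 10% imputed with complete data, and so adds the unavoidable loss from missing data to the loss from omitting the arms. The second part is under 4 points even at 10%.
- *That imputed death times will contradict known survival.* The plan does not say that death times are imputed. What can be said is that the imputed variable is undefined and that last contact is not a listed predictor.
- *That the primary and SOFA imputations contradict each other.* The SOFA rule deals with scores missing because of death, which is a different problem. The contrast is an argument for consistency and not an error in itself.
- *That a diluted interaction test would hide the four-cell results.* The plan reports them either way, in the main report or as supplementary material. The test changes emphasis only.

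**Conclusion.** The point holds in a limited form. As written, the imputation model for the primary outcome leaves out terms that the primary model estimates and tests, and this biases both log hazard ratios and the interaction toward zero by roughly m. The practical size depends wholly on m, which the article does not give: negligible at 1–2%, modest at 5%, and worth avoiding at 10%.

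The figures rest on four assumptions: the outcome itself is what is imputed, imputed patients have mortality similar to the others, the events formula applies to the adjusted frailty model, and an imputed patient contributes no observed follow-up. Where partial follow-up is known and used, the dilution is smaller. If only a discharge date were imputed, the dilution argument would not apply in this form. The correction is nearly free and should be made before database lock, but the omission does not threaten the validity of a positive result.

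**What to change.** In the Primary outcome analysis section:

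1. Add fluid arm, speed arm and their product to the chained-equations predictors, in line with the use of the arms for SOFA.
2. State which variable is imputed and which rule applies first when a patient lacks both discharge information and 90-day follow-up.
3. Require imputed outcomes to be consistent with any known survival time, so that no patient is imputed as dead before a day on which he or she was known to be alive.
4. Report, as a sensitivity analysis, the version that censors these patients at last contact without imputation.
5. Report the number imputed by arm, so that readers can judge m.

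Event-indicator and cumulative-hazard terms are not needed. They serve the imputation of missing covariates in a Cox model, whereas here the outcome is what is missing.

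The cost is a few sentences of SAP wording, three extra terms in the imputation model and one further model fit. Allocation is known for every randomised patient. Item 3 may need a draw conditional on survival to last contact, which is somewhat more work than adding predictors, but only if event times are imputed.

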### Secondary outcomes

The following secondary endpoint analysis were defined:

- Renal replacement therapy up to 90 days.- Acute renal failure incidence defined as Kidney Disease Improving Global Outcomes (KDIGO)^(8)^ stage 2 or 3 evaluated at days 3 and 7. We plan to use both serum creatinine and diuresis for the KDIGO classification. Diuresis was collected on a daily basis during BaSICS, and therefore we will use the average diuresis over 24 hours as the urinary output criteria in KDIGO; creatinine criteria will be used if diuresis information is not registered. In case of a disagreement between creatinine and diuresis criteria for KDIGO, we will consider the worst criteria.- SOFA score assessed both as the total value and as individual components and each of their components separately (Cardiovascular, Neurologic, Coagulation, Hepatic and Respiratory) will be evaluated on day 3 and 7.- Mechanical ventilation-free days within 28 days.

Renal replacement therapy up to 90 days will be estimated using a mixed Poisson model adjusted for age, baseline SOFA and admission type and will be reported as the incidence per 1,000 patient-days. Alternatively, we will also report renal replacement therapy at 90 days in a competing risk model considering death as a competitor for the need for RRT. Incidence of AKI at days 3 and 7 will be tested with mixed generalized linear models with a binomial distribution and the logit link function (also known as a mixed logistic regression model^(9)^) considering site as a random effect; the results will be presented with odds ratios and 95% confidence intervals. Additional analysis combining KDIGO and death will be performed as a supportive analysis to address competitive risks issues.

SOFA score will be tested with a mixed generalized linear model using the distribution that best fits the data (Poisson, gamma, inverse gaussian, or multinomial, among others), and the results will be presented as the mean and/or median differences or ratios with respective 95% confidence intervals using the delta method. Organ dysfunctions at day 3 and 7 (specific SOFA item - cardiovascular, neurologic, coagulation and respiratory as a dichotomous variable defined as higher than 2) will be tested with mixed logistic regression models.

Total SOFA score will be missing if patients died before the measurement time point , and multiple imputation by chain equations using the *mice* R^(10)^ package shall be performed to address the competitive risk bias. Acquired SOFA trend and baseline characteristics will be considered to predict any missed SOFA scores at 3 and 7 days, with the study arms as covariates. Sensitivity analysis without the arms as covariates shall also be performed.

Mechanical ventilation-free days within 28 days will be tested considering the proportion of ventilator-free days in that time frame using zero/one inflated beta or beta-binomial regression assuming zero free-days for those patients who died within that period independently of the amount of time the patient actually used the ventilator. We will consider as ventilation day any day where the patient received any duration of mechanical ventilation. Effect measures shall be presented as the absolute mean difference.

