#### Exclusion criteria

Were excluded: patients age < 18 years; acute renal failure treated with renal replacement therapy (RRT) or expected to require RRT within the next 6 hours; severe electrolyte disturbances (serum sodium ≤ 120mmol/L or ≥ 160mmol/L); death considered imminent and inevitable within 24 hours; with suspected or confirmed brain death; under exclusive palliative care and those previously enrolled in the BaSICS study

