### Planned statistical analysis for the primary, secondary and tertiary endpoints

All clinical endpoints shall be presented as similar as possible to those shown in table 2. Categorical variables will be presented as the number and percentage. Continuous variables will be presented as the mean and standard deviation for variables such as age and physiological parameters (blood pressure, sodium and potassium levels). We will favor the presentation of ordinal variables, such as Sequential Organ Failure Assessment (SOFA) score, as the median and interquartile range. An alpha of 5% and 95% confidence intervals will be used unless otherwise stated; similarly, all analyses will be based on the intention-to-treat principle unless otherwise stated. Analyses will be performed with the latest R version available at the end of the patients’ follow-up (most probably version 4.0).

**Table 2 t2:** Outcomes comparing slow versus fast infusion speed and Plasma-Lyte versus 0.9% sodium chloride

Characteristics	Plasma-Lyte	0.9% Sodium chloride	Effect measure	p value*	Slow infusion	Rapid infusion	Effect measure	p value†	p value‡
			(95%CI)		(n = xxx)	(n = xxx)	(95%CI)		
Primary outcome									
90-day mortality	xx.x (xx.x)	xx.x (xx.x)	x.xx (x.xx - x.xx)	x.xx	xx.x (xx.x)	xx.x (xx.x)	x.xx (x.xx - x.xx)	x.xx	x.xx
Secondary outcomes									
Acute renal failure with need for renal replacement therapy within 90 days									
Incidence (per 1000 patient-day)	xx.x	xx.x	x.xx (x.xx - x.xx)	x.xx	xx.x	xx.x	x.xx (x.xx - x.xx)	x.xx	x.xx
At day 1	xx.x (xx.x)	xx.x (xx.x)		-	xx.x (xx.x)	xx.x (xx.x)		-	-
At day 2	xx.x (xx.x)	xx.x (xx.x)		-	xx.x (xx.x)	xx.x (xx.x)		-	-
At day 3	xx.x (xx.x)	xx.x (xx.x)		-	xx.x (xx.x)	xx.x (xx.x)		-	-
At day 7	xx.x (xx.x)	xx.x (xx.x)		-	xx.x (xx.x)	xx.x (xx.x)		-	-
In hospital (at least one renal substitution in hospital stay)	xx.x (xx.x)	xx.x (xx.x)	x.xx (x.xx - x.xx)	x.xx	xx.x (xx.x)	xx.x (xx.x)	x.xx (x.xx - x.xx)	x.xx	x.xx
Unknown at 90-day follow up	xx.x (xx.x)	xx.x (xx.x)		-	xx.x (xx.x)	xx.x (xx.x)		-	-
Lost contact for 90-day follow-up	xx.x (xx.x)	xx.x (xx.x)		-	xx.x (xx.x)	xx.x (xx.x)		-	-
Incident renal failure (using KDIGO ≥ 2) at day 3	xx.x (xx.x)	xx.x (xx.x)	x.xx (x.xx - x.xx)	x.xx	xx.x (xx.x)	xx.x (xx.x)	x.xx (x.xx - x.xx)	x.xx	x.xx
KDIGO ≥ 2 or death at day 3	xx.x (xx.x)	xx.x (xx.x)	x.xx (x.xx - x.xx)	x.xx	xx.x (xx.x)	xx.x (xx.x)	x.xx (x.xx - x.xx)	x.xx	x.xx

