### Tertiary outcomes

We defined tertiary endpoints that should be considered exploratory:

Intensive care unit (ICU) and hospital mortality will be tested with mixed logistic regression models considering site as the random effect and adjusted for the same variables used in the primary analysis.Length of stay in the ICU and in the hospital will be compared with mixed generalized linear models with a Poisson distribution and a logarithm link, also considering site as the random intercept effect.Quality of life six months after ICU discharge will be analyzed in a 10% sample using EQ-5D-3L questionnaires.^(11)^ This will be reported separately in a different manuscript.

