### Subgroup analyses

Subgroup analyses will be performed with mixed effects Cox proportional hazard models for the primary outcome. We intend to report interaction p-values and hazard ratios of Plasma-Lyte against Saline and Slow against Rapid infusion in each subgroup:

Patients with and without sepsis, defined using Sepsis 3 criteria.^(2)^Patients with baseline KDIGO 1 and those ≥ 2.Surgical and nonsurgical patients.Patients with or without traumatic brain injury.Patients with Acute Physiology and Chronic Health Evaluation II (APACHE II)^(12)^ ≥ 25 and < 25 points.Patients who received > 1.000mL *versus* ≤ 1.000mL in the 24 hours before randomization.

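### AKI, SOFA, organ-dysfunction and ventilator-free-day models name no baseline covariates, and AKI is labelled incident but defined as status at day 3 or 7

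*SAP article*

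**What the plan says.** The primary model (SAP article, Primary outcome analysis) is a mixed-effects Cox model with site as random effect, adjusted for age, baseline SOFA and type of admission. Under Secondary outcomes, the RRT model is "adjusted for age, baseline SOFA and admission type and will be reported as the incidence per 1,000 patient-days". Under Tertiary outcomes, ICU and hospital mortality are "adjusted for the same variables used in the primary analysis".

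The other secondary models are specified differently. The AKI model is logistic, "considering site as a random effect; the results will be presented with odds ratios and 95% confidence intervals", and no fixed covariate is listed. The total SOFA, organ-dysfunction (SOFA item above 2) and ventilator-free-day models list no covariates.

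The AKI endpoint is "Acute renal failure incidence defined as Kidney Disease Improving Global Outcomes (KDIGO)^(8)^ stage 2 or 3 evaluated at days 3 and 7", and Table 2 labels it "Incident renal failure (using KDIGO ≥ 2) at day 3", with a matching row for day 7. No rule about baseline KDIGO accompanies either. The general rule is that "all analyses will be based on the intention-to-treat principle unless otherwise stated". The only renal exclusion at entry is "acute renal failure treated with renal replacement therapy (RRT) or expected to require RRT within the next 6 hours", and one planned subgroup comparison is "Patients with baseline KDIGO 1 and those ≥ 2".

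**The concern.** There are two separate problems.

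The first is uneven adjustment. The plan fixes covariates model by model and names them where it wants them, and no general sentence extends the primary set to the remaining secondary models. Followed as written, day-3 SOFA is compared without baseline SOFA, although baseline SOFA is used to adjust mortality and RRT. The stake is precision on the organ-function endpoints, from data the trial already holds.

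The second is a mismatch between label and definition. An incident event needs a patient free of the condition at the start. The definition describes a state at day 3 or day 7 and does not say who is at risk. Patients can enter already at KDIGO ≥ 2, so the text supports two different endpoints. One is new AKI among those without it. The other is KDIGO ≥ 2 status among everyone. If the choice stays open, it can be made after results are known, which the SAP's introduction says it aims to prevent.

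**Working it through.** **Stated figure.** The document gives no power, rate or correlation for these endpoints. Its only such figure is the primary power of 89%. With 5,500 patients per margin, 35% control mortality and a hazard ratio of 0.9, the expected deaths are 5,500 × 0.35 + 5,500 × (1 − 0.65^0.9) = 3,693. Power is Φ(√(3,693/4) × |ln 0.9| − 1.96) = 0.893. The stated figure reproduces, and this point does not affect it.

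**Models side by side.**

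| Outcome | Site effect | Baseline covariates named |
|---|---|---|
| 90-day mortality | random | age, baseline SOFA, admission type |
| RRT to 90 days | mixed model, effect not named | age, baseline SOFA, admission type |
| ICU/hospital mortality | random | as primary |
| AKI, days 3 and 7 | random | none |
| Total SOFA, days 3 and 7 | mixed model, effect not named | none in the comparison; baseline data used for imputation |
| Organ dysfunction (SOFA item > 2) | mixed model, effect not named | none |
| Ventilator-free days | not named | none |

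**Label against definition.** (a) The label says incident. (b) The definition is KDIGO 2 or 3 at day 3 or 7. (c) The default population is everyone randomised. (d) KDIGO 2 or 3 without current or imminent RRT is not excluded, and baseline KDIGO ≥ 2 is a planned subgroup. Taken together, (b), (c) and (d) mean that a patient at KDIGO ≥ 2 on entry and still there on day 3 is an event. This contradicts (a).

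**Illustrative dilution.** Every rate here is an assumption. Let b be the share at KDIGO ≥ 2 at baseline and s the fraction of these still ≥ 2 at day 3, taken as equal in both arms (no fluid effect on recovery). Let a = 20% be control incidence in patients at risk, with a true risk ratio of 0.90.

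- Control risk, all patients: A = b·s + (1 − b)·a
- Treated risk, all patients: C = b·s + (1 − b)·0.9a
- At-risk odds ratio: (0.18/0.82)/(0.20/0.80) = 0.878
- Power: Φ(|A − C|/SE − 1.96), with 5,500 per arm for all patients and 5,500 × (1 − b) for patients at risk

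Example, b = 10% and s = 60%: A = 0.06 + 0.18 = 0.240 and C = 0.06 + 0.162 = 0.222. The odds ratio is (0.222/0.778)/(0.240/0.760) = 0.904. Baseline cases make up 0.06/0.24 = 25% of control events.

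Results for s = 60–80%:

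| b | Baseline cases among control events | All-patient OR | Power, all patients, unadjusted | Power, at risk only |
|---|---|---|---|---|
| 5% | 14–17% | 0.892–0.895 | 67–69% | 74% |
| 10% | 25–31% | 0.904–0.909 | 59–61% | 72% |
| 20% | 43–50% | 0.922–0.928 | 44–47% | 67% |
| 30% | 56–63% | 0.937–0.942 | 33–35% | 61% |

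With a = 10%, the at-risk odds ratio is 0.890 and the all-patient odds ratio runs from 0.914 to 0.968 over the same values of b and s.

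**Illustrative precision for SOFA.** In a linear model, adjusting for a baseline with correlation ρ multiplies the variance by 1 − ρ². For assumed ρ of 0.3, 0.5 and 0.7 the factor is 0.91, 0.75 and 0.51. An effect with 80% power unadjusted would then have power Φ((1.96 + 0.84)/√(1 − ρ²) − 1.96) = 84%, 90% and 98%. The SAP allows Poisson, gamma and other distributions for SOFA, so this shows direction only. It does not carry over to the logistic or beta-type models.

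**The case against.** The strongest reply is that nothing here is invalid. Under randomisation an unadjusted comparison is unbiased and keeps its error rate, and no stated power is undermined. That stands: a reader might infer that the treatment comparisons are biased, and the document does not support that.

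A second reply is that silence in a condensed article is not a decision against covariates. This has some force for SOFA, organ dysfunction and ventilator-free days, whose model descriptions are brief. It has less for AKI, where the sentence names a model term and stops, directly after the RRT model with its covariates listed.

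Three further inferences go too far:

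- **That the plan decides to count existing AKI as incident.** No sentence says so. It follows from the definition plus the intention-to-treat default, and the word incident points the other way. The supportable statement is that label and definition conflict.
- **That every one of these models ignores the outcome's baseline value.** Ventilator-free days accrue after randomisation and have no baseline value. The relevant omissions are baseline ventilation status and the common covariates.
- **That baseline information is unused for SOFA.** It enters the imputation of missing scores, and the separate exploratory Bayesian network is illustrated with a baseline state. Neither adjusts the main comparison.

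Finally, if fluid affects recovery from existing AKI, including those patients gives a legitimate but different estimand. This is correct. It is a reason to name the estimand, and it limits the dilution argument to the case of no effect on recovery.

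**Conclusion.** The point holds in two limited parts, both confined to secondary endpoints.

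First, covariates are specified unevenly. Read as written, AKI, SOFA, organ dysfunction and ventilator-free days give up precision that baseline data already collected could supply, without bias to the randomised comparison. The gain cannot be quantified from the document.

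Second, the AKI label and definition conflict. Taken literally, persistent baseline AKI counts as incident. If fluid does not affect recovery, an effect on new AKI is diluted. Under the assumptions shown (control incidence 20%, baseline share 5–30%, persistence 60–80%), the odds ratio moves from 0.878 to between 0.892 and 0.942. These figures are illustrations, because the document gives neither AKI rates nor SOFA correlations.

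**What to change.** **Covariates.** State that all secondary models are adjusted for age, baseline SOFA (the component score for component outcomes) and admission type, with site as random effect. Add baseline KDIGO stage or creatinine for AKI, and baseline ventilation status for ventilator-free days.

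**AKI endpoint.** Choose one of two wordings and use it in both the text and Table 2:

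1. Keep all randomised patients, rename the endpoint KDIGO ≥ 2 at day 3 and at day 7, adjust for baseline stage, and report incident AKI in patients with baseline KDIGO < 2 alongside; or
2. Define incident AKI explicitly in patients with baseline KDIGO < 2, with the all-patient analysis adjusted for baseline stage as supportive.

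The second option restricts on a characteristic fixed before randomisation, so the arms remain comparable.

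**Cost.** This is a change of SAP wording before database lock. Creatinine, SOFA and ventilation status are in Table 1, and the planned renal subgroup already needs baseline KDIGO stage. The incident-AKI denominator becomes smaller. The adjusted odds ratios are conditional on the added covariates rather than marginal over them, which the report should state.
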